#### 2.3.3. Informed Consent and Patient Withdrawal Criteria

Volunteers will be freely given a copy of the patient information sheet and informed consent form, either in the English or Malay language, prior to signing the informed consent form. The study team will explain the study details and inform the subjects that they could withdraw from the study at any time without giving any reason. In addition, subjects could discontinue from the study if they suffered from significant illness or violation of the protocol. The patient information sheet included a subject confidentiality clause to protect confidentiality before, during, and after the trial. Only the ethics committee and regulatory authority could access the trial-related data and they were always required to respect confidentiality. In addition, the results of the completed study were published without the disclosure of the subject’s identity. A copy of the signed informed consent form was given to the subject.

#### 2.3.4. Assignment of Intervention, Randomisation, and Blinding

The three-period, six-sequence, permuted block randomisation sequence will be generated using statistical software SAS Enterprise Guide version 7.1, SAS Institute Inc., Cary, NC, USA. The seed code 736522 was generated for the purpose of reproducibility, and the source code is attached in Supplementary Figure S2. The randomisation code will be given to the pharmacist to perform the investigated product dispensing for three formulations: code A for metformin 1000 mg, code B for AP capsules 1000 mg, and code C for AP capsules 2000 mg.

Both the metformin tablets and AP capsules are registered with the Ministry of Health Malaysia. The investigational product accountability was recorded by the pharmacist. Dispensing activities were performed according to the line clearance procedures to avoid cross contamination or dispensing errors (Supplementary Figure S3). Another pharmacist will monitor each dispensing activity and a duplicate sticker labelled with the investigational product name (Supplementary Figure S4), protocol number, and other details will be attached to the envelope.

This will be an open-label pharmacokinetics and metabolomics study. Prior knowledge of the investigational product administration to the subject does not affect the bioavailability and metabolic effects of the drug. The blinding procedure will not be applied in this study so the investigator and the subjects are aware of the type of investigational products being administered during the clinical trials.

#### 2.3.5. Investigational Products Intervention

The subjects will be divided into two stations during the administration procedure of the investigational products (Supplementary Figure S5). Subjects are either given metformin 1000 mg tablets, AP 1000 mg, or AP 2000 mg at each period according to the randomisation schedule (Figure 3). Subjects will be instructed to swallow the study drug without chewing with 240 mL of plain water at room temperature in the presence of the principal investigator. The label from the drug envelope will be stuck directly to the case report form and the actual time will be recorded immediately after the mouth is checked to ensure that all of the drugs have been administered. Subjects will not be allowed to drink water one hour before and two hours after the study drug administration. After dosing, subjects will be required to remain in a sitting or semi-reclining position for at least 4 h; subjects will also be restricted from taking part in any stressful physical activity.

#### 2.3.6. Sample Size Calculation

This is a proof-of-concept pharmacokinetics and pharmacometabolomics exploration study to determine the pharmacokinetic parameters and human metabolic pathways. The objective of a pharmacokinetics study in a phase I trial is to mainly measure the characteristic of the drug, so there is no statistical basis to determine the sample size. The number of subjects usually ranges from 4 to 24 subjects [38]. The United States guidance recommended a minimum of 12 subjects at each arm in the pharmacokinetics bioequivalence study [39]. Another sample size estimation approach for metabolomic analysis without the experimental pilot data proposed 12 subjects in each group using dynamic probabilistic principal component analysis or 18 subjects in each group for the probabilistic principal components and covariates analysis [40]. This study will recruit 18 subjects in each formulation considering the phase one features and analyses to plan for the pharmacokinetics and metabolomics.

#### 2.3.7. Screening and Data Collection

Subjects will be screened for the eligibility criteria according to the screening case report form after signing the informed consent form. The principal investigator will perform the physical examination, review the demographic data, electrocardiogram, vital signs, biochemistry, haematological, serological, urinalysis test, and perform the interview questionnaire to determine the subject’s eligibility. Eligible subjects will attend the dosing day at the trial site and will be asked to fast for at least ten hours to reduce the variability of drug absorption. Eligible subjects will then be asked to attend a method validation visit to collect additional blood and urine samples.

On the dosing day, the study coordinator will record the subject attendance list, subject enrolment list, subject identification list, and subject randomisation sheet. Subjects will be assigned to the randomisation group by the study coordinator. Pre-dose urine samples and plasma samples will be collected before dosing. After single-dose oral administration, fourteen blood samples will be collected at 0.5, 1, 1.5, 2, 2.5, 3, 3.5, 4, 5, 6, 8, 10, 12, and 24 h post-dose. The actual sampling time will refer to the subject plasma sampling schedule (Supplementary Figure S6) and subject urine sampling schedule. An indwelling intravenous cannula will be used to collect the pre-dose and up to 12 h post-dose blood sample by syringe. The blood samples will then transferred into a pre-labelled potassium ethylenediaminetetraacetic acid (KEDTA) tube. The heparin-lock technique will be performed to prevent clotting of the blood by injecting 1 mL of heparinised saline in the indwelling cannula. Ambulatory blood will be collected at 24 h post-dose. The blood samples will then be centrifuged at 35,000 rpm for 15 min at 20 °C, and the plasma separated into three aliquots in cryotubes and stored at −80 °C in a freezer. The post-dose urine samples will be collected at three periods: period U1 (0–4 h post-dose), U2 (4–8 h post-dose), and U3 (8–12 h post-dose. The urine samples will then be separated into three aliquots in cryotubes and stored at −80 °C in a freezer. The study activities will be recorded on the case report form.

Food intake will be standardized throughout ward stay. Subjects will be provided with lunch at 12.20 pm, a tea break at 4.30 pm, and dinner at 7 pm. The calorie count for the main meal will be maintained at approximately 600 kcal and the tea break calories at around 350 kcal. Meal intake start time and end time will be recorded on the meal monitoring form.

The biological samples will be segregated according to the individual subjects for all of the sampling time points and processing batches after the study is completed. The details of the plasma segregation activities will follow the procedures according to the plasma and urine sample segregation forms.

### 2.4. Safety Assessment

The principal investigator will stay on-site to monitor any adverse events during the ward stay. Vital signs will be monitored every two hours at 10 a.m., 12 p.m. and 2 p.m. Any complaint from the subjects will be directly recorded into the case report form for adverse event classification. An adverse event that occurs will be classified according to the clinical safety data management guidance [41].

Stopping rules and the continual reassessment method should be applied to phase one dose-escalation trials [42,43,44]. However, the stopping rules will not be implemented in this study for the following reasons: the investigated products are registered medicines, and the administered dose will be according to the regulatory approved dose. The study will involve antidiabetic drugs taken under the fasting condition, and lunch will be given four hours post-dose. Although metformin does not pose a hypoglycaemia risk, additional random plasma glucose monitoring will be performed every half an hour up to four hours to monitor the hypoglycaemia effect [45]. In the case a clinically significant hypoglycaemia event is determined by the investigator, 20 g of glucose water will be given to the subject at any point in time.

Physical examinations will be performed on all subjects before being discharged from the ward. At the end of the last dosing period, the biochemistry, haematology, and urinalysis will be performed to ensure the subjects’ safety before being discharged. A post-study phone call follow-up will be made seven days after the last dose of the last visit for adverse event monitoring.

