## Abstract

This protocol aims to profile the pharmacokinetics of metformin and *Andrographis paniculata* (AP) and continue with untargeted pharmacometabolomics analysis on pre-dose and post-dose samples to characterise the metabolomics profiling associated with the human metabolic pathways. This is a single-centre, open-labelled, three periods, crossover, randomised-controlled, single-dose oral administration pharmacokinetics and metabolomics trial of metformin 1000 mg (*n* = 18), AP 1000 mg (*n* = 18), or AP 2000 mg (*n* = 18) in healthy volunteers under the fasting condition. Subjects will be screened according to a list of inclusion and exclusion criteria. Investigational products will be administered according to the scheduled timeline. Vital signs and adverse events will be monitor periodically, and standardized meals will be provided to the subjects. Fifteen blood samples will be collected over 24 h, and four urine samples will be collected within a 12 h period. Onsite safety monitoring throughout the study and seven-day phone call safety follow-up will be compiled after the last dose of administration. The plasma samples will be analysed for the pharmacokinetics parameters to estimate the drug maximum plasma concentration. Untargeted metabolomic analysis between pre-dose and maximum plasma concentration (Cmax) samples will be performed for metabolomic profiling to identify the dysregulation of human metabolic pathways that link to the pharmacodynamics effects. The metformin arm will focus on the individualised Cmax plasma concentration for metabolomics study and used as a model drug. After this, an investigation of the dose-dependent effects will be performed between pre-dose samples and median Cmax concentration samples in the AP 1000 mg and AP 2000 mg arms for metabolomics study. The study protocol utilises a crossover study design to incorporate a metabolomics-based study into pharmacokinetics trial in the drug development program. The combination analyses will complement the interpretation of pharmacological effects according to the bioavailability of the drug.

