The phase one study aims to find an optimal dose through dose escalation in several cohorts [20]. This is a proof-of-concept study to explore the integration of the metabolomic study and the pharmacokinetic study in early-phase clinical trial. In the phase 1 trial, clinical monitoring, continuous laboratory parameters, and pharmacokinetics study are performed to determine dose-escalation. Metabolomic profiles obtained before, during, or after dosing provide insights about the drug mechanism of action and variation in the response to treatment [21]. The application of a metabolomic study in the early-phase clinical trial has the advantage of a small, short, and underpowered design, however, pharmacometabolomics can help reduce the variability of the study populations and act as a powerful surrogate of drug response in the identification of perturbed human metabolic pathways and explore provisional therapeutic or safety biomarkers [2].

In the bioanalytical analyses, metformin will be used as a model drug for individualised pharmacokinetic and metabolomic analyses to identify dysregulated human metabolic pathways. Then, AP arms will follow a similar analysis framework with an exploration of the additional dose-dependent effects. This study utilises a crossover design to reduce the intra-subject variability to compare the metabolomics of the metformin and AP formulations. Both medicines exhibit antidiabetic effects from the literature, so the human metabolic pathways related to antihyperglycemic effects using pharmacometabolomics will be explored.

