### Objectives

The study aimed to determine the safety of metformin 1000 mg, AP capsules 1000 mg, and AP capsules 2000 mg in the clinical part.

In the pharmacokinetics and metabolomics analyses, metformin 1000 mg will be used as a model drug for the determination of the pharmacokinetic parameters including the Cmax, Tmax, half-life (T1/2), and AUC0-infinity. The individualised Cmax of metformin will be used for the metabolomics analyses to identify dysregulated human metabolic pathways that are associated with diabetic effects.

The AP 1000 mg and AP 2000 mg analyses will follow the pharmacokinetics and metabolomics framework from the metformin arm in the second analysis. The pharmacokinetics for AP 1000 mg and AP 2000 mg will be compared for the three bioactive compounds, andrographolide, neoandrographolide, and deoxyandrographolide. The dysregulated human metabolic pathways identified from the metabolomics analyses for two doses will be compared based on the dose-dependent effects. 

Finally, the dysregulated human metabolic pathways associated with the diabetic effects will be compared for all three intervention arms.

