## 3. Data Collection, Management, and Statistical Analyses

### 3.1. Clinical Data

The clinical part will be mainly recorded in the case report form and the clinical laboratory results. After the study is completed, the principal investigator will sign off on each case report form and the data lock date will be confirmed. After the data lock is set, the data will be transcribed into a data management Excel sheet to monitor the data entry activity. The data management sheets will include the demographic data, vital signs, clinical laboratory data, actual sampling time points, dosing time points, and adverse events.

The forms and templates that will be used throughout the data collection, management, and statistical analyses are outlined in Figure 4. The subject demographic data and laboratory characteristics for screening and post-dose monitoring will be tabulated. The number of adverse drug reactions will also be recorded accordingly. A list of tables, listings, and figures will be generated for the study report (Supplementary Figure S7).

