## 4. Discussion

This proof-of-concept study protocol aims to determine the pharmacokinetics and explore the metabolomics profiling of metformin and AP capsules for application in early-phase clinical trial. The protocol describes the conduct of clinical trials with comprehensive methods and Supplementary Documents that comply with the principle of Good Clinical Practice and relevant trial-related forms to record the clinical outcomes.

The pharmacokinetics and bioavailability study could determine the rate and extent of the drug being absorbed into the human blood circulation [27]. From the first metformin analysis dataset, the individualised peak plasma concentration obtained from the pharmacokinetics study will be used to explore the human metabolic pathways. This approach can identify the dysregulated human metabolic pathways associated with the pharmacological effect accurately based on the peak plasma concentration of the drug. Therefore, the combination of a pharmacokinetics and pharmacometabolomics study could complement the interpretation of the human metabolic pathways during peak plasma concentration.

In the second phase analyses, the two doses of AP capsules arms provide additional information about the pharmacokinetics profiles characteristic of the three biomarkers, andrographolide, neoandrographolide, and deoxyandrographolide. The pharmacometabolomic analysis for the two doses of AP capsules potential identify dose-dependent metabolic signatures with intense metabolic features at affected human metabolic pathways associated with the pharmacodynamic effects.

This study will employ a crossover design instead of the typical 6 + 2 dose escalation first-in-human study design to reduce the variability of the trial subjects in metabolomic study, shorten the trial duration, and maximise the resources to recruit different subjects. The study protocol is practical for institutional academic research compared to complex industry sponsor regulatory trials while complying with the Good Clinical Practice principle. This study potential provides a framework for the application of a pharmacokinetics and metabolomics approach in a phase one trial, which could reveal valuable drug intervention dysregulated human metabolic pathways or molecular drug effects through metabolomics analyses.

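### Pathways are to be tied to diabetic and pharmacological effects, but the stated analysis contains no observed effect, and the half-hourly glucose already collected is not related to treatment or pathways

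*Protocol article*

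**What the plan says.** The aim is worded as an association with an effect in several places. The Abstract says the metabolomic comparison is meant "to identify the dysregulation of human metabolic pathways that link to the pharmacodynamics effects". The Objectives ask the metformin analysis to "identify dysregulated human metabolic pathways that are associated with diabetic effects", and end with a comparison in which "the dysregulated human metabolic pathways associated with the diabetic effects will be compared for all three intervention arms". The Discussion goes further: "This approach can identify the dysregulated human metabolic pathways associated with the pharmacological effect accurately based on the peak plasma concentration of the drug".

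The Introduction gives the source of the link. It says that the literature reports antidiabetic effects for both medicines, and continues "so the human metabolic pathways related to antihyperglycemic effects using pharmacometabolomics will be explored".

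The analysis is in section 3. Section 3.2 derives pharmacokinetic parameters from drug concentrations. Section 3.3 runs PCA, PLS-DA and a t-test between two time points, then maps the significant features to KEGG pathways. Section 3.1 covers clinical data, where "laboratory characteristics for screening and post-dose monitoring will be tabulated"; glucose is not named.

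Glucose appears only in section 2.4 (Safety Assessment): "additional random plasma glucose monitoring will be performed every half an hour up to four hours to monitor the hypoglycaemia effect".

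**The concern.** A t-test between pre-dose and peak shows that metabolites differed between two times. KEGG mapping shows which known pathways contain them. Neither step shows that an antihyperglycaemic effect occurred, or that a given pathway carried it. Followed as written, the plan lets a pathway be called diabetes-related because of its name and the drug's reputation.

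The design also leaves it uncertain whether glucose would move. The subjects are healthy men, fasted for at least ten hours (section 2.3.7), given single doses, with no meal until lunch four hours after dosing (section 2.4). Section 2.4 states that metformin carries no hypoglycaemia risk, and the glycaemic evidence cited for AP is an HbA1c change after 12 weeks (section 1).

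At stake is the trial's last objective, the comparison of diabetes-related pathways across the three treatments, and the dose comparison within AP. The one measured variable that bears directly on glycaemia has no stated part in either.

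**Working it through.** There is no figure in the plan to reproduce. Section 2.3.6 says that the sample size has no statistical basis, and no alpha, power or effect size is given. The check is a comparison of aims with analyses, then a count, then what n = 18 could deliver.

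**1. Aim against analysis**

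| Stated aim | Analysis that addresses it |
|---|---|
| Pharmacokinetics of metformin and three AP compounds | Section 3.2, non-compartmental analysis |
| Metabolite change, pre-dose to peak | Section 3.3, PCA, PLS-DA, t-test |
| Pathways affected | Section 3.3, KEGG mapping |
| Association with diabetic or pharmacodynamic effect | No glucose, insulin or other glycaemic variable is an endpoint, covariate or correlate |

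**2. Glucose times against blood samples.** Assuming the first reading is at 0.5 h, half-hourly to 4 h gives 0.5, 1, 1.5, 2, 2.5, 3, 3.5 and 4 h: 8 times. All 8 are on the post-dose blood grid of section 2.3.7. They span every quoted Tmax: 2 h (section 2.1) and 2.5 h (section 1) for metformin, and 1.63 to 2 h for AP (section 2.1). A sampled peak within 4 h therefore has a glucose value at the same nominal time. Maximum count: 18 subjects x 3 periods x 8 times = 432.

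**3. Precision of a treatment difference in mean 0-4 h glucose.** One summary per subject and period gives 54 values. Residual df = 54 - 1 - 17 (subjects) - 2 (periods) - 2 (treatments) = 32; sequence is absorbed by subject. The 95% half-width is t(0.975, 32) x SD x sqrt(2/18) = 2.037 x SD x 0.333. The within-subject SD is not in the document, so a range is assumed:

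- SD 0.2 mmol/L: 0.14 mmol/L
- SD 0.3 mmol/L: 0.20 mmol/L
- SD 0.4 mmol/L: 0.27 mmol/L

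**4. Detectable effects at n = 18** (assumed two-sided alpha 0.05, 80% power)

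- Paired difference: (1.960 + 0.842)/sqrt(18) = 0.66 SD of the paired differences by normal approximation; 0.70 SD by the noncentral t.
- Correlation between a metabolite change and glucose: tanh[(1.960 + 0.842)/sqrt(18 - 3)] = tanh(0.723) = 0.62, before any correction for the number of features.

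A treatment contrast in glucose is feasible. A correlation with pathways is weakly powered and can only be descriptive.

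**The case against.** The strongest reply has four parts.

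- **The source of the link is disclosed.** The Introduction attributes the antidiabetic effect to the literature and speaks of exploration. It also presents the metabolome as a surrogate of drug response. This stands: annotation is the visible plan, in a study that calls itself proof-of-concept. It does not support the Objectives' language of association or the Discussion's claim of accuracy.
- **Glucose may be reported.** Section 3.1 tabulates post-dose laboratory characteristics, and the full protocol and the list of tables are supplements not shown here. A reader might infer that the glucose data are discarded; the document does not support that. A table, however, would not relate glucose to treatment or pathways, and the mismatch between aims and analysis lies within the article's own text.
- **Glucose cannot carry much weight here.** All three treatments are active and there is no placebo or untreated period. If all lowered glucose equally, every contrast would be zero. No pre-dose glucose is stated, and a change from pre-dose is mixed with the effect of continued fasting. Any glucose water given would disturb later values. A reader might infer from step 3 of the working that the trial could show or rule out an acute effect. It could not: the interval concerns differences between treatments only. Nor should a pathway be called associated only where glucose moves, since flat glucose in fasted healthy men would not show that the drug had no action.
- **Timing.** Section 3.4 says that the metformin analysis has been published. A glucose analysis added now is post hoc for that report. This stands.

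**Conclusion.** The point holds as a mismatch between claim and analysis, with a cheap improvement available. The objectives and Discussion promise pathways tied to diabetic or pharmacological effects. The stated analysis can deliver acute metabolite changes with literature-based annotation. Up to 432 glucose values, on the blood-sampling times and collected up to the lunch at four hours, have no stated analysis beyond possible tabulation.

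An exploratory glucose analysis would add within-subject evidence on differences between treatments, including AP 1000 mg against 2000 mg, to about 0.14 to 0.27 mmol/L under the assumed SDs. It would not establish or exclude an effect of any single product, and it does not justify a pass/fail rule for pathways. The conclusion assumes that the glucose schedule runs from dosing in every period and that all 18 subjects complete. The supplements might add a glucose analysis, but the wording in the article would still need to change.

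**What to change.** **Analysis (section 3).** Add an exploratory within-subject analysis of time-averaged 0-4 h plasma glucose:

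- Model with sequence, period, treatment and subject, adjusted for that period's pre-dose glucose where available. If it was not recorded, it could be measured in the pre-dose plasma already drawn.
- Report all treatment contrasts with 95% intervals, including AP 1000 mg versus 2000 mg.
- Describe the relation of each subject's glucose to changes in the candidate pathways, without significance claims, and note the |r| of about 0.62 needed for 80% power.
- Flag values recorded after any glucose water.
- State that without a placebo period the analysis estimates only differences between treatments, and label it post hoc for the metformin report already published.
- Do not use glucose as a pass/fail gate for pathways.

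**Wording (Abstract, Objectives, Discussion).** Report pathways as acute single-dose changes in fasted healthy men, with hypothesis-generating annotation to diabetes-related pathways. Remove the claim of accuracy from the Discussion.

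**Cost.** Data entry, one extra exploratory model and, if needed, a glucose assay on stored pre-dose plasma. No new sampling. The price is a narrower claim.
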